### 2.4. Study Procedures

The recruitment period was planned from April 2021 to December 2023. Depending on risk stratification, patients undergo 18–49 visits, including the screening and the 12 follow-up visits (one every 3 months over the 36-month follow-up period).

At screening, the following data are collected: demographic and clinical characteristics; physical examination findings; disease-specific data (histological subtype, stage, number of involved nodal areas, extranodal involvement); patient breakdown according to mEORTC criteria; laboratory test results, Eastern Cooperative Oncology Group (ECOG) performance status; and functional test results, including pregnancy testing.

At treatment visits, the following data are collected: all changes in symptoms, physical examination, laboratory results; treatments administered; and adverse events. Pregnancy is verified at each treatment visit.

Collected information data during follow-up visits include date and extension of relapse in case of treatment failure; subsequent lymphoma treatment; secondary malignancies, cardio-vascular disease, and other organ toxicity; and survival.

Patients achieving complete metabolic response (CMR) on both PET-2 and end-of-treatment PET (EoT-PET) by blinded independent central review (see below) will undergo routine follow-up: clinical and laboratory evaluations every 3 months for the first 3 years, and additionally, a cfDNA assay (every 3 months during the first year, and every 6 months during the second year). PET imaging is performed only when indicated by clinical symptoms or laboratory abnormalities. If PET suggests HL relapse, a biopsy is strongly recommended to confirm the diagnosis of disease recurrence. Patients meeting criteria for limited relapse are included in group 2 and receive “delayed” INRT followed by nivolumab 240 mg every 14 days for 1 year.

Routine clinical data will be documented at study sites and entered into a secure, web-based electronic case report form (eCRF) system (The diCELLa eCRF Clinical Trials platform) (https://dicella.com/ecrf/ assessed on 14 August 2026). Documentation is sourced from routine medical records and verified for completeness through centralized and on-site monitoring by medical managers and clinical monitors. Imaging data and cfDNA are integrated with clinical data in the eCRF.

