In patients treated with nivolumab, the final (end-of-treatment) PET/CT was scheduled approximately four weeks after the last nivolumab dose. According to the protocol, this assessment was to be interpreted using the LYRIC criteria. In the case of an indeterminate response (IR), the PET/CT scan is reviewed in consensus by the reviewers to confirm IR. PET/CT in follow-up is recommended only in the following situations: clinical suspicion of relapse (appearance of symptoms or new findings on physical examination); reappearance of cfDNA after previous negative result; a 2-log increase in cfDNA in the blood.

CfDNA is measured at baseline and after two chemotherapy cycles (PET-2) in all patients. In addition, in LR patients entering CMR, cfDNA is assessed every three months during the first year and every six months during the second year.

Peripheral blood samples (20 mL) are collected in cell-free DNA BCT tubes (Streck) and centralized at the Institute of Oncology Research ([name] Lab). Plasma is processed to obtain at least 30 ng of cfDNA (~5000 genome equivalents), and germline genomic DNA (gDNA) is isolated from peripheral blood mononuclear cells. Longitudinal assessment of cfDNA for genotyping and residual disease quantification is performed using the LyV4.0 CAPP-seq assay (Cancer Personalized Profiling by Deep Sequencing) (CAPP-seq) [24]. The assay targets 344 kb of genomic space, including 33 Activation-Induced Cytidine Deaminase (AID)-associated somatic hypermutation (SHM) noncoding regions [25,26,27] and coding regions of 155 recurrently mutated genes in mature B-cell tumors. A complete list of the targeted genes and genomic regions, together with the analytical validation of the assay, has been previously reported (Pirosa et al., Supplementary Material) [24].

To ensure genomic fidelity and mitigate batch biases, patient-derived cfDNA and matched gDNA were sequenced simultaneously. Sequencing was performed on the Illumina NextSeq500 platform (paired-end, 2 × 150 bp). This paired approach, combined with background-error suppression models derived from healthy cohorts, enabled the precise isolation of true somatic mutations while filtering out inherited polymorphisms and sequencing artifacts (detailed bioinformatics and laboratory methodologies are described elsewhere).

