The third secondary endpoint is 3-year overall survival (OS) of the entire cohort of patients enrolled into the study, defined as time from patient registration to death for any reason. The OS will be estimated using the Kaplan–Meier method, with a two-sided 95% CI based on Greenwood’s standard error.

As this is a single-arm evaluation, analyses of the secondary endpoints will be descriptive and will report point estimates with corresponding measures of precision, without formal hypothesis testing against a concurrent comparator. The summary of the study outcomes is presented in Table 1.

Finally, the diagnostic performance of cfDNA for detection of an impending relapse during follow-up in LR group patients will be summarized using overall accuracy, sensitivity, specificity, negative predictive value, and positive predictive value. Each metric will be presented as a point estimate with a two-sided 95% CI computed using the Clopper–Pearson exact method.

As an intention-to-treat (ITT) approach is preferred for phase III randomized clinical trials and a per protocol (PP) approach is preferred for equivalence and non-inferiority trials, a PP analysis will be preferred for assessing the primary study endpoint of treatment efficacy in LR patients, and an ITT approach will be used as secondary [30]. For all the other study endpoints in the RAFTING study, both an ITT and PP will be used.

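### cfDNA accuracy is planned as simple proportions, although sampling stops at about month 24 of a 36-month follow-up and a cfDNA rise can itself prompt the PET that finds relapse

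*Protocol article*

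**What the plan says.** Section 2.6 of the protocol article states that "the diagnostic performance of cfDNA for detection of an impending relapse during follow-up in LR group patients will be summarized using overall accuracy", together with sensitivity, specificity and the two predictive values, and that "Each metric will be presented as a point estimate with a two-sided 95% CI computed using the Clopper–Pearson exact method". No prediction window, relapse horizon or unit of analysis is attached. The right-censoring rule in Section 2.7 covers the primary and other time-to-event endpoints, so it does not reach these measures.

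Section 2.4 gives the surrounding design:

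- **Sampling.** In LR patients in complete metabolic response, "cfDNA is assessed every three months during the first year and every six months during the second year". That is about six follow-up samples, at roughly months 3, 6, 9, 12, 18 and 24.
- **Follow-up.** Clinical visits continue every 3 months to month 36.
- **Reference test.** "PET imaging is performed only when indicated by clinical symptoms or laboratory abnormalities". Besides clinical suspicion, the stated reasons for a follow-up PET are "reappearance of cfDNA after previous negative result; a 2-log increase in cfDNA in the blood". If PET suggests relapse, biopsy is strongly recommended.

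The Discussion calls the use of cfDNA exploratory, and Table 1 does not list it among the outcomes.

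**The concern.** The stated method suits one index test and one independently obtained reference result per patient. The design departs from that in three ways.

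1. **Horizon.** Read literally, relapse during follow-up includes year 3, when no sample is taken. Scoring those relapses as cfDNA misses lowers sensitivity and NPV, whatever the marker can do.
2. **Verification.** A cfDNA-positive patient without symptoms is referred for PET. A cfDNA-negative patient without symptoms is not. If some cfDNA-negative relapses stay unfound at data cut-off, sensitivity and NPV come out too high.
3. **Unit.** With about six samples per patient, a per-sample table and a per-patient table can give very different specificity. The Clopper–Pearson interval assumes independent units, which repeated samples from one patient are not.

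The article presents cfDNA as a possible basis for earlier intervention, and only about 10 LR relapses are expected. With so few, the choice of horizon and unit could decide the reported result.

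**Working it through.** **The plan's own figures.** The article gives no cfDNA accuracy figure. Section 2.5 gives the LR sample size, which fixes how many relapses to expect:

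- n = (z0.80 + z0.80)² × 0.90 × 0.10 / (0.90 − 0.85)² = 2.833 × 0.09 / 0.0025 = 102.0, so 102.
- Total = 102 / 0.75 / 0.85 = 160.

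Both reproduce. At 90% 3-year PFS, 102 × 0.10 = 10.2 events are expected (5.1 at 95%, 15.3 at 85%). PFS events include deaths, so 10 relapses is an upper figure. An observed 8/10 has an exact 95% interval of 44% to 97%, and 7/10 one of 35% to 93%.

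**Sampling gap (assumed constant hazard).** S(t) = 0.90^(t/36), so S(24) = 0.9322, S(30) = 0.9159 and S(36) = 0.9000.

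- Share after month 24: (0.9322 − 0.9000) / 0.1000 = 32%. With no credit for lead time, a perfect marker reaches at most 68%.
- Share after month 30: (0.9159 − 0.9000) / 0.1000 = 16%. If the month-24 sample is credited for 6 months ahead, the ceiling is 84%.
- If sampling is timed from the end of two to four 28-day cycles but relapse is counted to 36 months from registration, the last sample falls at about month 26 to 28. The share after it is then 27% to 21%.

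**Size of each bias (illustration).** Assumed: true sensitivity 80%, specificity 95%, 10.2 relapses among 102 patients, no drop-off.

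(a) A share f of relapses falls after month 24, and these are cfDNA-positive only at the 5% false-positive rate. Sensitivity = 0.80(1 − f) + 0.05f.

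| f | Sensitivity | NPV | Specificity |
|---|---|---|---|
| 0% | 80.0% | 97.7% | 95.0% |
| 10% | 72.5% | 96.9% | 95.0% |
| 20% | 65.0% | 96.1% | 95.0% |
| 30% | 57.5% | 95.3% | 95.0% |

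(b) A share v of cfDNA-negative relapses is found by cut-off, and the rest are counted as true negatives. Sensitivity = 0.80 / (0.80 + 0.20v).

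| v | Sensitivity | NPV | Specificity |
|---|---|---|---|
| 100% | 80.0% | 97.7% | 95.0% |
| 90% | 81.6% | 97.9% | 95.0% |
| 75% | 84.2% | 98.3% | 95.0% |
| 50% | 88.9% | 98.9% | 95.1% |

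(c) Both together (f from 10% to 30%, v from 50% to 100%): sensitivity 57.5% to 84.1%, NPV 95.3% to 98.4%, specificity 95.0% to 95.1%.

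**Unit of analysis.** With 95% specificity per sample, six samples and any positive counting, per-patient specificity is 0.95⁶ = 74% if false positives are independent and 95% if they are fully correlated. At 98% per sample the range is 0.98⁶ = 89% to 98%.

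**The case against.** The best defence is that a condensed article may leave window and unit to an analysis plan that is not shown. With one row per patient and a sensible horizon, the Clopper–Pearson interval is valid. Nor are cfDNA-negative patients abandoned: visits run to month 36, symptoms and physical findings also lead to PET, and biopsy is strongly recommended. Verification is differential, not absent. All of this stands, and it limits the point. It does not remove it, because the article does fix a method and a target, and applied as written they score relapses that had no sample near them and ignore how PET was triggered.

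Four stronger readings are tempting and not supported:

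- **That the measures will be wrong.** The size depends on late-relapse and missed-relapse shares that the documents do not give, and the two biases partly offset each other.
- **That 68% is the ceiling.** It needs a constant hazard, a 36-month horizon and no credit for lead time.
- **That specificity is badly biased.** The two mechanisms move it by about 0.1 point. The 74% figure arises only from the unit of analysis, with independent false positives.
- **That relapses found on symptom-prompted PET give an unbiased sensitivity.** cfDNA-positive relapses tend to be scanned first and leave that subset. With true sensitivity 80% and a share q of cfDNA-positive relapses still symptom-prompted, subset sensitivity is 0.8q / (0.8q + 0.2): 29%, 50% and 67% for q = 10%, 25% and 50%.

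**Conclusion.** The point holds as a risk of bias and a mismatch between method and design, not as a demonstrated error. Under the illustrative assumptions, the sampling gap lowers sensitivity by about 7.5 points for each 10% of relapses after month 24. Trigger-dependent verification raises it by about 2 to 9 points when 10% to 50% of cfDNA-negative relapses go unfound. NPV moves by at most about 2.4 points. A reader of the results could not tell which bias dominates. Specificity depends on the unit, by up to 21 points at 95% per sample.

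The wide interval from about 10 relapses is a limit of the data and not a fault of the method. The aim is exploratory, and the primary test of 3-year PFS does not use these measures. The change is worth making but is not critical.

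**What to change.** - Define the target as relapse within a fixed window after each sample, for example 6 months (the longest sampling gap), and count only relapses up to that window after the last scheduled sample.
- Estimate sensitivity, specificity and predictive values on patient-visits, allowing for censoring, with intervals from a patient-level bootstrap. Keep Clopper–Pearson for summaries with one row per patient, labelled as such.
- Tabulate what prompted each follow-up PET (symptoms or findings, cfDNA, other laboratory change). Do not present sensitivity among symptom-prompted PETs as unbiased.
- Add a sensitivity analysis that varies the share of unfound relapses among unverified cfDNA-negative patients, for example from 0% to 50%.

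Cost: no new samples or scans, and the Discussion says that follow-up is ongoing. The reason for each PET must be derived from the records, since the follow-up data items listed in Section 2.4 do not name it. Fewer relapses enter the analysis: under the constant hazard about 10.2 × 0.84 = 8.6 instead of 10.2, so intervals widen.

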## 2. Methods and Analysis

### 2.1. Study Design

The RAFTING trial (NCT04866654, EudraCT 2020-002382-33) is a prospective, multicenter, international (Poland, Italy, Spain), single-arm, non-inferiority, phase 2 study.

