### 2.5. Sample Size

The sample size calculation was based on the following assumptions: the anticipated 3-year progression-free survival (PFS) rate for stage I–IIA non-bulky eHL patients with a negative PET-2, treated with CMT, is 94% [6]; the expected 3-year PFS for PET-2-negative patients with similar clinical characteristics, treated with chemotherapy alone comprising two to four courses of chemotherapy, ranges between 87% and 93%, as reported in three prospective and one retrospective clinical trials, despite variations in patient characteristics and treatment intensity [6,7,8,28].

The expected 3-year PFS for PET-2-negative patients with TMTV < 84 mL treated with chemotherapy alone is anticipated to be at least 90%. In this context, a one-sample non-inferiority design was employed to calculate the sample size required to test whether the proportion of low-risk eHL patients, treated with chemotherapy alone, alive and disease-free at 3 years, is non-inferior to that of patients treated with CMT. For the non-inferiority assessment of the primary endpoint, we assumed an expected true response proportion of 90%. The non-inferiority historical reference value was set at 95%, reflecting the historical outcome of CMT reported in trials such as RAPID and H10, with an absolute non-inferiority margin of 10 percentage points; thus, non-inferiority would be concluded if the response proportion in the study population exceeds 85%.

To define the sample size of patients to be enrolled, we used a one-sided type I error of 0.20 and type II error of 0.20 (80% power). “The one-sided α of 0.20 was prespecified because the study was designed as an exploratory Phase 2 screening trial, in which minimizing false-negative findings was prioritized over controlling false-positive findings, consistent with the recommendations of Rubinstein et al.” [29].

A total of 102 low-risk (defined by a low MTV and a negative PET-2) eHL patients should be enrolled to exclude a difference between the true proportion and the comparison value of at least 10%. Considering an expected 75% of patients with a negative PET-2 and low TMTV, and a drop-off rate of 15%, 160 patients had to be enrolled in the trial.

In the exploratory phase 2 setting, a one-sided α = 0.20 was chosen because the potential harm of a false negative result (failing to recognize an effective treatment) is considered more significant than that of a false positive result (proceeding to confirmatory testing) [29].

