### 2.6. Statistical Methods Used to Compare Groups for Primary and Secondary Outcomes

The primary efficacy endpoint is 3-year progression-free survival (PFS) in the LR group, which will be evaluated for non-inferiority relative to a prespecified historical control rate. The PFS in the LR group is defined as the time from LR patient registration to the first occurrence of disease progression (limited or extended relapse) or death for any reason. The PFS distribution will be estimated using the Kaplan–Meier product-limit method, and the standard error of the 3-year survival estimate will be computed using Greenwood’s formula. For the primary hypothesis, a one-sided 80% confidence interval (CI) for the 3-year PFS rate will be constructed. Non-inferiority will be concluded if the lower bound of this one-sided 80% CI exceeds 85%, corresponding to a one-sided type I error rate (alpha) of 0.20.

The first secondary endpoint is also used for LR patients only. The 3-year freedom from second treatment failure (FF2TF) is calculated for LR who have limited relapse only and are rescued according to the protocol. It is measured from registration to the date of second relapse (during or after RT followed by nivolumab) (extended relapse) or death for any reason. FF2TF will be estimated using the Kaplan–Meier method, and the 3-year FF2TF estimate will be reported with a two-sided 95% confidence interval (CI) derived using Greenwood’s formula.

The second secondary efficacy endpoint is the 3-year PFS in the HR cohort, defined as the time from HR patient registration to the first occurrence of disease progression (extended relapse) or death for any reason. The 3-year PFS estimate will be obtained from the Kaplan–Meier curve, with a two-sided 95% CI calculated using Greenwood’s formula.

Both secondary assessments will allow us to calculate 3-year event-free survival (EFS) across the entire study cohort. The EFS is defined as the time from patient registration to the failure of the planned study treatment, which varies by study groups and includes only extended relapses or death for any reason. This is considered one of the most important study aims, reflecting the efficacy of a flexible-intensity and personalized treatment offered to different eHL prognostic groups. The 3-year EFS estimate will be obtained from the Kaplan–Meier curve, with a two-sided 95% CI calculated using Greenwood’s formula.

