Nonetheless, the protocol faces important challenges. The complexity of the study design may lead to deviations in treatment or procedures. Another very important limitation is the single-arm design and reliance on comparison with a historical control. Such comparisons may be influenced by temporal changes in chemotherapy application, supportive care, imaging and RT techniques, and other aspects of clinical practice. However, the standard first-line treatment of eHL, based on chemotherapy with PET-adapted strategies, has remained largely unchanged over the past two decades, with stable results, including a 3-year PFS of 95%. Improvements in supportive care are unlikely to have substantially influenced PFS. The influence of improvements in imaging and RT techniques cannot be ruled out in a single-arm study with a historical comparator. We selected the RAPID trial as the principal historical benchmark because it represents a well-characterized PET-adapted cohort with similar, although not identical, eligibility criteria and RT technique (INRT). In addition, response assessment in the comparator studies was performed using blinded independent central review, reducing variability in PET interpretation, as in the RAFTING study. Nevertheless, advances in PET/CT acquisition, reconstruction algorithms, scanner performance, and staging procedures over time may have influenced patient classification and outcome assessment. Therefore, comparisons with historical controls should be interpreted with caution, and our findings require confirmation in prospective randomized or contemporaneous comparative studies. Another limitation of the study is related to future implementation of the study results, related to potential variability in imaging interpretation in the real-world setting, particularly regarding the assessment of PET-2 and baseline TMTV. The central review process has been implemented to minimize this risk in the study. Moreover, the BICR of a given test is needed when the study endpoint depends directly on this test [23]. The real-world application of these criteria may lead to inconsistencies across treatment centers. Similarly, the use of cfDNA as a biomarker, although highly promising, remains exploratory, and definitive conclusions may be limited by inherent variability in assay sensitivity and specificity. Additional challenges relate to the details of the treatment protocol. The initially planned schedule of 24 nivolumab doses may prove difficult to achieve in all patients, and available data suggest that shorter treatment courses might still provide adequate disease control in this setting.

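### Per-protocol is made the deciding set by a two-arm convention; in a single-arm test against a fixed 85% it is not reliably the conservative one

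*Protocol article*

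**What the plan says.** Section 2.1 describes a "single-arm, non-inferiority, phase 2 study". Section 2.5 sets the historical reference at 95% and the margin at 10 points, which gives a fixed threshold of 85%, with a "one-sided type I error of 0.20 and type II error of 0.20 (80% power"). The decision rule in section 2.6 reads: "Non-inferiority will be concluded if the lower bound of this one-sided 80% CI exceeds 85"%.

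The end of section 2.6 then chooses the analysis set. The reason given is that "a per protocol (PP) approach is preferred for equivalence and non-inferiority trials". From this the article concludes that "a PP analysis will be preferred for assessing the primary study endpoint of treatment efficacy in LR patients". Of the alternative for this endpoint it says only that "an ITT approach will be used as secondary". No reason specific to a single-arm design is offered, although the same section calls the study a single-arm evaluation. Nothing requires the ITT result to meet the 85% criterion as well.

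Two other statements bear on how many patients might be excluded. The Discussion warns that "The complexity of the study design may lead to deviations in treatment or procedures", but later reports that every patient finished the planned treatment.

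**The concern.** In a randomised non-inferiority trial, non-adherence and crossover tend to make two arms look alike, so ITT can favour the claim and PP guards against that. Here no between-arm difference exists to shrink; the low-risk (LR) PFS is compared with a constant. What PP does in this setting is remove patients for reasons arising after they were assigned to LR. If those reasons are linked to poor outcome, the estimate moves towards success, and the set chosen for caution becomes the permissive one.

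At stake is the trial's only formal test. With PP preferred and ITT not required to pass, a disagreement between the two would be settled in favour of PP.

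**Working it through.** **Inputs.** From section 2.5: null rate 0.85, expected rate 0.90, one-sided alpha 0.20, power 0.80, 102 LR patients, 75% LR share, 15% drop-off, 160 enrolled. From section 2.6: Kaplan–Meier estimate, Greenwood standard error, one-sided 80% lower bound. My assumptions: no censoring before 3 years, so that Kaplan–Meier with Greenwood reduces to a proportion with its Wald standard error; 102 patients analysed; and the excluded fractions and their PFS, which the article does not give.

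**1. The plan's own figures reproduce.** n = (0.8416 + 0.8416)² × 0.90 × 0.10 / (0.90 − 0.85)² = 101.999, so 102. Then 102 / 0.75 = 136 and 136 / 0.85 = 160. The 15% therefore enters as an inflation of total enrolment.

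**2. Where the pass limit lies.** Lower bound = p − 0.8416 × √(p(1 − p)/n).
- 12 events in 102: 0.8824 − 0.8416 × 0.0319 = 0.8555, passes.
- 13 events in 102: 0.8725 − 0.8416 × 0.0330 = 0.8448, fails.

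The rule at n = 102 is thus at least 90 event-free patients. At a true rate of 85%, the binomial probability of 90 or more is 0.223. This is the baseline with no exclusions; it differs from the nominal 0.20 because the count is discrete and the bound approximate.

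**3. How few exclusions change the answer.**

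| All assigned | Lower bound | After dropping patients with events | Lower bound |
|---|---|---|---|
| 13/102 | 84.48% (fails) | one dropped: 12/101 | 85.41% (passes) |
| 14/102 | 83.41% (fails) | two dropped: 12/100 | 85.27% (passes) |
| 15/102 | 82.34% (fails) | three dropped: 12/99 | 85.12% (passes) |

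**4. Chance of a claim when the true LR rate is exactly 85%.** If a fraction d with PFS q is excluded, the rate among those kept is (0.85 − d·q)/(1 − d). The chance of a claim is the probability of at least 90 event-free among 102 at that rate.

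| Excluded (d) | Their PFS (q) | Rate in PP set | Chance of a claim |
|---|---|---|---|
| none | – | 85.0% | 0.22 |
| 2% | 75% | (0.85 − 0.015)/0.98 = 85.2% | 0.24 |
| 5% | 75% | (0.85 − 0.0375)/0.95 = 85.5% | 0.27 |
| 10% | 75% | (0.85 − 0.075)/0.90 = 86.1% | 0.33 |
| 15% | 95% | (0.85 − 0.1425)/0.85 = 83.2% | 0.11 |

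**5. Check by simulation.** With 120 assigned LR patients (160 × 0.75) and a true rate of 85%, the claim rate is 0.19 with no exclusions and 0.23 when 10% of patients with and without events are excluded alike. It is 0.29 when 10% of patients with events and 5% of those without are excluded, and 0.12 when the figures are 5% and 15%. Exclusion unrelated to outcome leaves the error near nominal; exclusion related to outcome moves it, in either direction.

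**The case against.** The strongest reply is that PP has a genuine single-arm purpose here. The question is how LR patients do on chemotherapy alone. If some receive off-protocol radiotherapy, the all-assigned set includes the very treatment being omitted, and its PFS may drift up towards the 95% benchmark; PP removes that. This stands. It means that neither set is safe alone, and it rules out saying that ITT is always the stricter set or that the error rate holds only when excluded patients fare exactly like those kept: if they fare better, the error falls.

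The design also limits how exclusions could arise. A positive PET-2 places a patient in the high-risk group. Group 1a has no planned treatment left once classed LR, because PET-2 is also its end-of-treatment scan (section 2.4). Patients lost to follow-up or withdrawing consent are right-censored at their last assessment (section 2.7), not removed. The Discussion reports that all patients finished treatment. These points stand and lower the likely size. They leave exclusions for eligibility, allocation or procedural deviations, and at the boundary one is enough.

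A reader might take "a drop-off rate of 15"% as the PP exclusion rate and conclude that the error doubles: 15% excluded at 75% or 70% PFS would give 0.40 or 0.50. The article does not support this. The figure inflates total enrolment, is not described as PP exclusion among LR patients, and no PFS for excluded patients is stated.

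Finally, ITT is prespecified as secondary and the trial is presented as exploratory, with confirmation needed. A disagreement would be visible, but the article does not let it alter the conclusion. That the article does not define the PP set is not held against it; the full protocol may do so.

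**Conclusion.** The concern holds as a should-fix. The reason given for making PP primary does not carry over to a single-arm comparison with a fixed 85%, and the set that decides the claim can be the more favourable of the two. Under the assumptions above, the false-claim probability rises from 0.22 to between 0.24 and 0.33 for 2% to 10% excluded at 75% PFS; it drops below nominal if the excluded patients do better. With completion as reported, the lower end is the more plausible for treatment-related exclusions. The article does not show that bias has occurred or that its direction is known. The fault is not that the set forms after treatment begins, since LR status itself depends on PET-2; it lies in exclusions made after that assignment.

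**What to change.** In section 2.6, define the primary set as all patients centrally assigned to LR (TMTV below 84 mL and negative PET-2), analysed regardless of treatment later received. Conclude non-inferiority only if the one-sided 80% lower bound exceeds 85% in that set and in the PP set. Delete the sentence that supports PP by reference to equivalence and non-inferiority trials in general. Follow-up was still under way when the article was written, so the change is best made before the primary result is known.

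Both analyses are already planned, and 102 and 160 stay as they are under the plan's formula. Requiring both sets to pass lowers power somewhat from the 0.78 that a single set of 102 has at a true rate of 90% (probability of at least 90 event-free). The loss should be small if few patients are excluded, because the two sets then nearly coincide; it cannot be put as a figure without an exclusion rate.
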